## Abstract

**Background:**

Care for seniors is complex because patients often have more than one disease, one medication, and one physician. It is a key challenge for primary care physicians to structure the various aspects of each patient’s care, to integrate each patient’s preferences, and to maintain a long-term overview. This article describes the design for the development and feasibility testing of the clinical decision support system (CDSS) eCare*Seniors© which is electronic health record (EHR)-based allowing for a long-term, comprehensive, evidence-based, and patient preference-oriented management of multimorbid seniors.

**Methods/design:**

This mixed-methods study is designed in three steps. First, focus groups and practice observations will be conducted to develop criteria for software design from a physicians’ and practice assistants’ perspective. Second, based on these criteria, a CDSS prototype will be developed. Third, the prototype’s feasibility will be tested by five primary care practices in the care of 30 multimorbid seniors. Primary outcome is the usability of the software measured by the validated system usability scale (SUS) after 3 months. Secondary outcomes are the (a) willingness to routinely use the CDSS, (b) degree of utilization of the CDSS, (c) acceptance of the CDSS, (d) willingness of the physicians to purchase the CDSS, and (e) willingness of the practice assistants to use the CDSS in the long term. These outcomes will be measured using semi-structured interviews and software usage data. If the SUS score reaches ≥70 %, feasibility testing will be judged successful. Otherwise, the CDSS prototype will be refined according to the users’ needs and retested by the physicians and practice assistants until it is fully adapted to their requirements and reaches a usability score ≥70 %.

**Discussion:**

The study will support the development of a CDSS which is primary care-defined, user-friendly, easy-to-comprehend, workflow-oriented, and comprehensive. The software will assist physicians and practices in their long-term, individualized care for multimorbid seniors.

**Trial registration:**

German Clinical Trials Register, DRKS00008777

## Background

Primary care for seniors is complex because patients often have more than one disease, one medication, and one physician. Population-based studies show that 55–98 % of seniors (≥65 years of age) exhibit multimorbidity [1], meaning that they have more than one chronic disease [2]. This disease burden results in an average intake of 3.6 different pharmacological agents per day: 33 % of the seniors meet the criteria for polypharmacy (defined by the World Health Organization as five or more substances) and 65 % of them take five to seven different agents daily [3]. The medications most frequently prescribed in this age group are used for widespread diseases such as hypertension, coronary heart disease, cardiac insufficiency, chronic stomach problems, and diabetes [4]. From a physician’s perspective, the demographic development with the aging of populations, the differentiation of modern medicine with evolving therapeutic options, and the diversity of patients’ choices increase the complexity of health care management for this age group.

A survey among primary care physicians showed that physicians are willing to accept a clinical decision support system (CDSS) when it is designed to support their care for elderly patients with multiple chronic diseases and/or polypharmacy [5]. Yet, although medical informatics is considered to have this potential, the current practice administration systems are typically not geared to handle this complexity as they focus on billing and treatment documentation, while their orientation on complexity, quality of care, and longitudinal personalized care is poor. Existing CDSSs showed inconsistent results on care processes and patient outcomes when evaluated in randomized controlled trials. For example, a CDSS generating guideline-based reminders for appropriate antihypertensive drug classes improved medication selection but did not affect patients’ blood pressure [6]. Asthma care improved when providing guideline-based decision support, patient-specific alerts, and a referral option if asthma lacked control [7]. In contrast, an electronic health record (EHR)-based CDSS for diabetes which suggested individually tailored therapeutic changes, laboratory tests, and adequate follow-up intervals optimized glucose and systolic blood pressure control only marginally [8].

Besides the conceptual problem that the current CDSSs typically focus on a single chronic disease and do not address complexity, studies identified various technological, human, and organizational barriers for their acceptance. Technological barriers comprise poor system usability and user-friendliness, while human barriers relate to the lack of computer skills and physicians’ concerns regarding the loss of autonomy in clinical reasoning and/or decision-making power. Also, they are concerned about negative effects on the physician-patient relationship [9–11]. On the organizational level, physicians worry that systems lack integration into workflows but create additional workload [10, 11]. Recently, these drawbacks shifted the approach in health information technology development towards the early involvement of the target physician population [9, 11].

This manuscript presents the study design for the development and feasibility testing of the health care management software eCare*Seniors© which will be designed as a CDSS for the long-term, comprehensive, evidence-based, and individualized health care management of multimorbid seniors. Integrating various strategies and functionalities, this CDSS will assist primary care physicians and practice teams in care processes. The idea and the initial concept were developed and tested as a practice-specific solution in one model practice [12].

Extending the prior concept, the purpose of this study is the development and feasibility testing of a new primary care-defined, EHR-based, software for the long-term management of seniors. The objectives are to (a) further develop the CDSS based on criteria according to the needs of primary care physicians and practice assistants, (b) test the feasibility of the new CDSS in real-life primary care by predefined outcome measures in a mixed-methods study, (c) offer a process evaluation addressing barriers and facilitators for implementation of the CDSS, and (d) provide a description of the CDSS to be tested in a future confirmatory study.

## Methods/design

### Study design

The study is designed as a mixed-methods study in primary care academic teaching practices of the University of Duisburg-Essen, Germany. Following recommendations on health information technology usability evaluation and the framework for the development of complex interventions, the software will be developed in three steps [13, 14]:Step 1: specification of the needs for the setting and usersA series of focus group sessions with primary care physicians and practice assistants as well as practice observations will be conducted to determine setting- and user-specific requirements. (Note: in the German health care system, the term ‘practice assistant’ refers to practice personnel who are typically graduates from a certified 3-year vocational training. They assume tasks in practice organization and patient management).Step 2: software developmentBased on the concept developed in the model practice and the requirements identified in the focus groups, a software prototype will be designed. This will be pretested by primary care physicians and practice assistants with subsequent modifications as indicated by the pretesting.Step 3: integration of the software into the settingTo test the new software prototype in routine primary care, a feasibility study will be performed in real-life practice scenarios. If the feasibility testing indicates the need for modification, the software will be refined accordingly.

Figure 1 provides an overview of the objectives, tasks, and target groups for the three steps.

**Fig. 1 Fig1:**
[figure not shown]
Flow chart of the study conduct

### Concept of the health care management software

The software eCare*Seniors© aims at overcoming deficits of the current software solutions for primary care. The logic follows the typical process of health care management for multimorbid seniors in primary care: (1) compilation and updating of all health care and health care process-related aspects in three categories: chronic care, prevention, communication, and organization [12]; (2) evidence-based assignment of priorities based on patients’ quality of life and mortality aspects; (3) integration of patients’ preferences by the assignment of health care priorities in agreement with the patient; (4) long-term individualized health care planning; and (5) support of everyday decision-making and practice processes for individualized health care management. The software solution aims at supporting German primary care physicians typically working in physician-owned practices with one to five physicians yet is applicable to other settings as well. The software is designed as a patient-centered, workflow-oriented platform which integrates responsibilities of physicians and practice assistants. The concept of the software solution integrates components of the chronic care model [15–17] and aims at practice redesign with optimized care processes for multimorbid seniors.

### Description of the user interface

The software has two key features: a physician module (physician control center) and a patient-centered visualization strategy (patient management center).

The first feature is a control center for the physician(s) responsible for practice management and the design of care processes. This control center is important to address potential physicians’ concerns regarding a loss of autonomy in clinical reasoning and/or decision-making power. The software offers choices for various settings in a higher-level structure which are based on epidemiologic data from our prior study, literature data on seniors’ care needs, and evidence-based recommendations. The options refer to the patients to be managed with the software (e.g., if the software is used for all seniors or special subgroups only), the spectrum of outcome-relevant conditions selected for management (e.g., if a physician prioritizes hypertension and diabetes care, while excluding other diseases), the degree of comprehensiveness (e.g., if disease-related and other aspects of care such as the availability of advanced directives or the involvement of a nursing service are included), the level of detail used for the patient-centered visualization (e.g., if chronic renal failure is presented as general information or detailed according to the stage of renal failure). An electronic tutorial will inform physicians about the software and its options and guide through the selection process for practice-specific configurations. This physician control center can be accessed at any time to newly define choices either by adding, refining, or removing options. For practices starting to use the software, an outcome-oriented ‘standard configuration’ is suggested. As the software leads to standardization and redesign of practice processes, it is important that the physician(s) in charge can determine the content and time sequence of quality processes suggested by the software. This helps to avoid excessive workloads and subsequent frustration of physicians and personnel using the software. For better system control in larger health care settings, a directory of setting-specific users’ rights and access codes will be integrated into the physician control center. The rights to access and edit information within the software will thus be structured hierarchically: physicians as administrators will define custom settings in the physician control center and assign user-specific rights depending on the professional and their individual role in practice care processes.

The second key feature of the software is the patient management center which applies a patient-centered visualization strategy: the various aspects of patients’ care will be highlighted in a new graphical user interface with symbols which are a combination of a colored field and a short keyword (so-called flags). This strategy is based on the semiotic triangle (Fig. 2) [18], a concept which is well-known in the field of linguistics. Two types of flags will be used. Information flags will provide relevant, patient-centered information, e.g., relevant diagnoses and medications. Dynamic action flags will indicate quality deficits (e.g., if patients’ blood pressure is not controlled) and refer to upcoming preventive and/or therapeutic measures (e.g., preventive measures, monitoring of a medication blood level). Figure 3 provides an example for the patient-centered visualization strategy.

**Fig. 2 Fig2:**
[figure not shown]
Model of the semiotic triangle

**Fig. 3 Fig3:**
[figure not shown]
Example of the patient-centered visualization strategy of eCare*Seniors© with information flags (chronic diseases, medication) and dynamic action flags (upcoming preventive and therapeutic measures)

The information source for the flags is each patient’s EHR: copied information will be exported and then newly edited using this flag system. The software will not evaluate or interpret any patient data by itself. All flags, including priorities and triggers for dynamic flags, will be selected by physicians themselves, either on an individual (one patient) or group (multiple patients) level. Depending on the rights assigned by the administrator, practice assistants will be entitled to apply dynamic flags for individual care processes in the patient management center, e.g., check-up or immunization intervals. When opening a patient’s EHR, the user interface of the software will automatically pop up in a separate window and provide the physician-selected flags for this individual patient’s health care management.

### Technical classification as CDSS

Depending on the human-computer interaction, a CDSS can undertake different functions in the process of decision-making: reminder, advisor, critic, or pilot [11, 19, 20]. Our software will integrate the four CDSS functions:It will visualize relevant aspects of each patient’s care using the information flags (reminder).It will provide physician-specified dynamic action flags for age- and sex-specific preventive measures, for diagnosis-specific measures (e.g., follow-up care after cancer treatment), and/or for predefined patient groups (advisor).It will point at quality deficits by providing dynamic action flags, e.g., if patients’ blood pressure is not controlled (critic).It will intuitively guide the user through the system (pilot).

Similar to other CDSSs, eCare*Seniors© combines the characteristics of an individually tailored approach and the characteristics of a population-based quality management system [11].

### Conduct of the study

#### Step 1: specification of the needs for the setting and users

##### Practice recruitment

The first step of the study will be conducted in the teaching and research practice network of our institute consisting of 185 primary care practices located in North Rhine-Westphalia, Germany. All practices are requested to take part in one of the two network meetings of the institute yearly. At one of these practice meetings, physicians will be informed about the study which requires the participation in two focus group sessions and one practice observation. Physicians who are interested in participating will be asked to sign up during the meeting. Interested physicians will be contacted by phone. For the focus groups and practice observations, we will recruit six physicians with up to two practice assistants each. This number is reasonable because the practices are similar to other practices in size, aim, and content of their work [21] belonging to the Association of Statutory Health Insurance Physicians North Rhine and Westphalia-Lippe. No inclusion and exclusion criteria for the practices will be defined.

##### Definition of CDSS criteria

First, a systematic literature search on recent studies including systematic literature reviews and meta-analyses will be conducted to identify CDSS functions described as effective in prior studies and to identify barriers and facilitators for using CDSSs in primary care practices. This information is needed to circumvent ineffective functionalities and to adequately address potential barriers for software utilization. Additionally, a search on population-based disease statistics and on guidelines for the treatment of common chronic diseases will be conducted. This is needed to program the various information and action flags within the software solution.

Second, two focus group sessions with primary care physicians and practice assistants from our practice network and practice observations will be conducted. The focus group sessions will be carried out in a mixed disciplinary group, i.e., physicians and practice assistants together, with a maximum of 15 persons per group. They will be facilitated by physicians and research team members of our institute. The current concept of eCare*Seniors© will be presented and discussed to identify requirements necessary to provide long-term optimized care for multimorbid seniors. Both focus group sessions will be audio-recorded.

Third, additional structured practice observations of everyday practice routines will be performed in the practices of those physicians participating in the focus group sessions. The observations will be carried out by a research team member of our institute and aim at better understanding which patient-related processes need to be addressed in the software. Based on a fictitious clinical vignette of a multimorbid senior, it will be documented whether the practices use specific markers in the EHR to track defined contents of care and patient characteristics, what kind of markers they use, how they are reminded of special contents of care, and who is responsible for applying and updating such markers. These practice observations will be recorded on a semi-structured documentation sheet which combines a simple checklist with free text items allowing for detailed comments on practice specifics.

##### Data analysis

Audio-recorded data of the focus groups will be transcribed. Structuring and coding of the focus group data and the free text items from the process observations will be performed in NVivo qualitative data analysis software, Version 10 (QSR International Pty Ltd., 2012). The coding scheme will be developed and refined over time by identifying categories directly from the transcripts and free text items. Both will be analyzed by two researchers. Quantitative data from the practice observations will be analyzed using simple frequency calculations. All statistical analyses will be performed using IBM SPSS Statistics for Windows, Version 22.0 (Armonk, New York: IBM Corp.).

The results from the focus groups and the practice observations will be specified in a set of criteria detailing the primary care requirements regarding the physician module and the patient-centered visualization strategy of the software. These criteria will provide the basis for the development of a prototype of eCare*Seniors©.

#### Step 2: software development

##### Software development

Based on the set of criteria defined in step 1, a prototype of the software will be developed by a company specialized in developing health information technology. The software will include an electronic interface which allows for interoperability with all certified practice administration software solutions available in Germany.

##### Pretesting

The software prototype will be tested by research team members of our institute and by the physicians and practice assistants who participated in step 1 of the study. The pretest will take place at our institute in Essen, Germany. Each participant will test the prototype for ten fictitious multimorbid seniors.

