##### Data collection

After pretesting, each participant will complete the validated system usability scale (SUS) [22] providing information on software usability, practicability, and user-friendliness. Additionally, information regarding software aspects that need to be improved will be provided using free text items.

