##### Data analysis

The usability of the prototype will be analyzed by determining the SUS score. The score can assume values between 0 and 40. To interpret the result in percent, each score will be multiplied by the factor 2.5 [22, 23]. Single item scores and the average overall score will be calculated. According to the literature, an overall SUS score ≥70 % denotes good usability, while a score ≤50 % indicates a considerable need for improvement [23]. Pretesting will be judged as successful when a SUS score of ≥70 % is reached. The free text items will be structured in NVivo qualitative data analysis software, Version 10 (QSR International Pty Ltd., 2012). The items will be analyzed using a coding scheme which will be developed and refined over time by identifying categories directly from the free text answers. Simple frequencies will be calculated for these categories. All statistical analyses will be performed using IBM SPSS Statistics for Windows, Version 22.0 (Armonk, New York: IBM Corp.).

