##### Software modification

If the SUS score and/or the free text items indicate the need to improve the prototype, a set of criteria for software revision will be defined based on these results. The prototype will be modified accordingly. Afterwards, researchers from our institute will check whether all modifications listed in the set of criteria have been adequately implemented and will finally approve the prototype. If not, the procedure of adapting the software and checking the modifications will be repeated until all criteria defined have been adequately addressed.

A written user manual illustrating the usage and functions of eCare*Seniors© will be created.

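### The Step 2 pretest SUS pools research-team ratings with those of the intended users, and a prototype modified after a low score is approved without a new user rating

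*Protocol article*

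**What the plan says.** All references are to the protocol article, Methods/design.

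- **Step 2, Pretesting.** The prototype "will be tested by research team members of our institute and by the physicians and practice assistants who participated in step 1". The section goes on: "Each participant will test the prototype for ten fictitious multimorbid seniors".
- **Step 2, Data collection.** "After pretesting, each participant will complete the validated system usability scale", and free-text items on needed improvements are collected as well.
- **Step 2, Data analysis.** Item scores and one average overall score are computed. No split by type of rater is mentioned. "Pretesting will be judged as successful when a SUS score of" at least 70 % is reached. A score of 50 % or less is described as a considerable need for improvement.
- **Step 2, Software modification.** If the SUS, the free text or both show a need, revision criteria are drawn up and the prototype is changed. Institute researchers then check whether the listed changes "have been adequately implemented and will finally approve the prototype". If the check fails, adapting and checking are repeated.
- **Study design.** The overview of Step 2 names primary care physicians and practice assistants as pretesters and does not mention the research team.
- **Step 3, Software refinement.** After a revision at that stage, the practice users test again and complete the SUS again.

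**The concern.** The Step 2 SUS is meant to show whether the prototype is usable for physicians and practice assistants. Two features of the text weaken it for that purpose.

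First, the average includes people who are not the users the software is built for. They belong to the institute that sets the criteria for the software. If they score it higher than practice staff do, the pretest can be called successful while the users' own average is below 70 %.

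Second, after a low score the only stated check is that the listed changes were made. That does not show that users now find the software usable. Step 3 does ask users to rate a revised version, so the two steps treat the same situation differently. The Discussion also says that end users are involved throughout all design steps, which fits poorly with approval by researchers alone.

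At stake are the meaning of the Step 2 result and the risk of taking a prototype of unknown usability into five practices.

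**Working it through.** **Scale check.** "The score can assume values between 0 and 40", and "each score will be multiplied by the factor 2.5". So 40 × 2.5 = 100, and 70 % corresponds to 70 / 2.5 = 28 raw points. The scale and the threshold are consistent.

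**Who is in the average.** Pretesting lists two groups of testers and then speaks of each participant. Data collection uses the same term for those who complete the SUS. No exclusion is stated, so the literal reading includes the team. The Study design section points the other way. The two sections need reconciling.

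**Number of users.** Step 1, Practice recruitment, plans six physicians with up to two assistants each. That gives N = 6 + (0 to 12) = 6 to 18 users.

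**Effect of pooling.** If m team members score d points above the users on average, the pooled mean exceeds the user mean by

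d × m / (N + m).

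N comes from the document. Both m (3 to 6) and d (10 to 20) are assumptions, because the document gives neither.

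| N users | m team | d points | Rise in mean |
|---|---|---|---|
| 18 | 3 | 10 | 30 / 21 = 1.4 |
| 18 | 6 | 20 | 120 / 24 = 5.0 |
| 12 | 6 | 20 | 120 / 18 = 6.7 |
| 6 | 3 | 10 | 30 / 9 = 3.3 |
| 6 | 6 | 20 | 120 / 12 = 10.0 |

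The range over these assumptions is about 1.4 to 10 points. If team members score like users (d = 0), the rise is zero.

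**Example.** With 12 users at a mean of 66 and 6 team members at 86, the pooled mean is (12 × 66 + 6 × 86) / 18 = 1308 / 18 = 72.7. The pretest passes although the users' mean is below 70.

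**Team raters needed to lift a failing user mean to 70.** The smallest number is N × (70 − user mean) / (team mean − 70), rounded up.

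| Assumed user mean | Assumed team mean | N = 6 | N = 12 | N = 18 |
|---|---|---|---|---|
| 68 | 85 | 1 | 2 | 3 |
| 65 | 85 | 2 | 4 | 6 |
| 60 | 80 | 6 | 12 | 18 |

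A near miss is reversed by a few raters. A clear failure needs as many team raters as users in the last row.

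**After a low score.** Both steps provide for modification against a set of criteria and for repetition until the criteria are met. Step 3 adds a new SUS from the users. Step 2 has only the researchers' check. The retest described in the Abstract follows feasibility testing, so it belongs to Step 3 and does not fill the gap.

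**The case against.** The case for leaving the plan alone has real substance.

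- **Pooling is a reading of the text.** The Study design section supports a user-only pretest, and the authors may have meant that. This stands as a reason to clarify. It does not remove the problem, because the detailed section is the one that would be followed.
- **The 70 % figure may not be a condition.** A reader might infer that it decides whether the software is installed in Step 3 practices. The document says only that pretesting is judged successful, and no section ties installation to the score. Step 2 is described as test-and-modify. This stands.
- **Users are still heard.** Free-text items can trigger revision even when the pooled average passes. This stands.
- **What goes forward has been changed.** A reader might infer that a prototype rated below 70 %, or even 50 % or less, goes unaltered into live practices. The text does not support that: a modified version goes forward, and its usability is unmeasured, not shown to be poor.
- **The people are not identified.** A reader might infer that the software's developers rate and approve their own work. The document has an outside company build the prototype. It names only the same institute for rating and approval, not the same individuals.
- **The primary outcome is separate.** It is the Step 3 SUS, rated by practice owners and assistants in five practices that were not in Steps 1 and/or 2. A Step 2 error does not bias it, and poor usability could show itself there. This stands and limits the importance of the point.

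**Conclusion.** The point holds in a limited form. As written, the Step 2 average mixes team and user ratings, in tension with the Study design section, and a version modified after a low score needs no new user rating. The Step 2 result may therefore not describe usability for physicians and practice assistants.

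The plausible distortion is about 1.4 to 10 SUS points. It rests on 6 to 18 users from the document, an assumed 3 to 6 team raters and an assumed 10 to 20 point difference. That the team scores higher is itself an assumption. The missing re-rating depends on none of these figures.

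The consequence is confined to the Step 2 conclusion and to what is known about the prototype on entry to Step 3. The point is worth correcting because the main change costs nothing, but it does not threaten the study's primary result.

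**What to change.** 1. **Whose SUS counts.** In Step 2, Data analysis, base the SUS and its 70 % judgement on the Step 1 physicians and practice assistants only. Use team members for technical checks and list any SUS they give separately. This costs nothing.
2. **Reconcile the sections.** Make Study design and Pretesting agree on who pretests and in what capacity. This is an edit to the text.
3. **After a low score.** In Software modification, choose one of two options:
   - have the same users give a brief repeat SUS on the modified prototype when their score is below 70 %, in line with Step 3; or
   - state that the Step 2 threshold is formative and is not a condition for Step 3.

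The repeat rating arises only after a failed pretest, and its cost is small if kept brief. Repeating the whole pretest would cost more: up to 18 practice staff would return to the institute, each working through ten fictitious patients. The second option is free.
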